## Synopsis

|                                    |                                                                                                                                                                                                                                                                                                                                                                                                                                                                                                                                                                                                                                                                                                                                                                                                                                                                                                                                                                                                                                                                                                                                                                                                                                                                                                                                                                                                                                                                                                                                                                                                                                                                                                                                                                                                           |
|------------------------------------|-----------------------------------------------------------------------------------------------------------------------------------------------------------------------------------------------------------------------------------------------------------------------------------------------------------------------------------------------------------------------------------------------------------------------------------------------------------------------------------------------------------------------------------------------------------------------------------------------------------------------------------------------------------------------------------------------------------------------------------------------------------------------------------------------------------------------------------------------------------------------------------------------------------------------------------------------------------------------------------------------------------------------------------------------------------------------------------------------------------------------------------------------------------------------------------------------------------------------------------------------------------------------------------------------------------------------------------------------------------------------------------------------------------------------------------------------------------------------------------------------------------------------------------------------------------------------------------------------------------------------------------------------------------------------------------------------------------------------------------------------------------------------------------------------------------|
| Title                       | A Phase IIb randomized, double-blind, controlled study of the efficacy against episodes of clinical malaria due to Plasmodium falciparum infection of GlaxoSmithKline Biologicals' candidate vaccine RTS,S/AS01E, administered IM according to a 0, 1, 2-month vaccination schedule in children aged 5 months to 17 months living in Tanzania and Kenya.                                                                                                                                                                                                                                                                                                                                                                                                                                                                                                                                                                                                                                                                                                                                                                                                                                                                                                                                                                                                                                                                                                                                                                                                                                                                                                                                                                                                                                           |
| Indication/Study population | Primary immunization of healthy male and female children aged 5 months to 17 months at enrolment, if eligible according to inclusion and exclusion criteria.                                                                                                                                                                                                                                                                                                                                                                                                                                                                                                                                                                                                                                                                                                                                                                                                                                                                                                                                                                                                                                                                                                                                                                                                                                                                                                                                                                                                                                                                                                                                                                                                                                              |

|                            | Freeze-dried fraction | Liquid fraction       |          |           |             |                                                                                    |
|----------------------------|-----------------------|-----------------------|----------|-----------|-------------|------------------------------------------------------------------------------------|
| Formulation                | RTS,S (µg)            |                       | MPL (µg) | QS21 (µg) | Dose Volume |                                                                                    |
| RTS,S/AS02A (0.5 mL dose)  | 50                    | Oil-in-water emulsion | 50       | 50        | 0.5 mL      | Efficacy against infection, Gambian adults (Malaria-005)                           |
| RTS,S/AS02A (0.25 mL dose) | 25                    | Oil-in-water emulsion | 25       | 25        | 0.25 mL     | Efficacy against clinical disease, Mozambican children (Malaria-026)               |
| RTS,S/AS02D                | 25                    | Oil-in-water emulsion | 25       | 25        | 0.5 mL      | Pediatric formulation (Malaria-034, -038, -040)                                    |
| RTS,S/AS01B                | 50                    | Liposomes             | 50       | 50        | 0.5 mL      | Efficacy in challenge model, adults (Malaria-027), endemic countries (Malaria-044) |
| RTS,S/AS01E                | 25                    | Liposomes             | 25       | 25        | 0.5 mL      | Proposed pediatric formulation (Malaria-046)                                       |

The vaccine will be further tested in younger children in a safety and immunogenicity trial in 5 to 17 month old children in Ghana (Malaria-047). The DSMB will review unblinded safety data from that trial to authorize progression to the proposed trial.

In this study, the efficacy of a three dose regimen of RTS,S/AS01E against clinical malaria disease due to infection with *P. falciparum* will be determined. Safety, reactogenicity and immunogenicity will be explored as secondary and tertiary objectives.

This product development plan is conducted under a partnership agreement with the Malaria Vaccine Initiative at PATH (MVI) and is guided by a joint MVI/GSK Steering Committee.

This study is overseen by a formally constituted DSMB operating under a charter.

**Objectives      Primary**

**NOTE:** *In the event that malaria rates are lower in the year of the study the cross sectional survey, unblinding and analysis scheduled at 4½ months post Dose 3 will be delayed until approximately 245 children have experienced an episode.*

- For RTS,S/AS01E when administered as 3 doses intramuscularly on a 0, 1, 2-month schedule to children aged 5 to 17 months living in malaria-endemic areas:
  - to assess efficacy against clinical malaria disease meeting the primary case definition (detected on active and passive case detection) with *P. falciparum* over a period of 4½ months (starting two weeks post Dose 3).

**Secondary**

**NOTE:** *In the event that malaria rates are lower in the year of the study the cross sectional survey, unblinding and analysis scheduled at 4½ months post Dose 3 will be delayed until approximately 245 children have experienced an episode.*

- For RTS,S/AS01E when administered as three doses intramuscularly on a 0, 1, 2-month schedule to children aged 5 to 17 months living in malaria-endemic areas:
  - to assess efficacy against clinical malaria disease meeting the secondary case definition (detected on active and passive case detection) with *P. falciparum* over a period of 4½ months (starting two weeks post Dose 3).
  - to assess safety and reactogenicity until 4½ months post Dose 3.
  - to assess the antibody responses to the hepatitis B surface (HBs) antigen up to 1 month post Dose 3.
  - to assess the antibody responses to the circumsporozoite (CS) antigen up to 4½ months post Dose 3.
  - to assess the T-cell immune response to CS antigen up to 1 month post Dose 3 in an Intracellular Cytokine Assay.
  - to assess the effect on hemoglobin, parasite prevalence and parasite density.

**Tertiary**

- For RTS,S/AS01E when administered as three doses intramuscularly on a 0, 1, 2-month schedule to children aged 5 to 17 months living in malaria-endemic areas:

- to assess efficacy against clinical malaria disease (detected on active and passive case detection) with *P. falciparum* over a period of 12 months post Dose 3.
- to assess safety between 4½ months post Dose 3 and 12 months post Dose 3.
- ***To assess safety until October 2008 in Kilifi and September 2008 in Korogwe.***

***Amended 17 April 2008***

- ***To assess efficacy against clinical malaria (detected on active and passive case detection) with P. falciparum from Dose 3 until October 2008 in Kilifi and September 2008 in Korogwe.***

***Amended 17 April 2008***

- to assess antibody responses to the circumsporozoite (CS) antigen at 12 months post Dose 3.
- to assess antibody responses to the hepatitis B surface (HBs) antigen at 12 months post Dose 3.
- ***to assess antibody responses to the circumsporozoite (CS) antigen at a cross-sectional survey occurring in October 2008 in Kilifi and September 2008 in Korogwe.***

***Amended 17 April 2008***

- to assess the T-cell immune response to CS antigen up to 12 months post Dose 3 in an Intracellular Cytokine Assay.

### **Exploratory**

- For RTS,S/AS01E when administered as three doses intramuscularly on a 0, 1, 2-month schedule to children aged 5 to 17 months living in malaria-endemic areas:
  - to evaluate the cellular immune responses to CS antigen up to 12 months post Dose 3 using cytokine elispot assay.
  - to evaluate the regulatory T-cell immune response to CS and blood stage malaria antigens at 4½ months post Dose 3.
  - to evaluate the humoral immune response to malaria blood stage antigens up to 12 months post Dose 3.

### **Study design**

- Experimental design: Phase IIb, two-center, double blind (observer blind, participant blind), randomized (1:1 ratio), controlled trial with two groups.
- Healthy male and female children aged 5 to 17 months will be screened; those determined to be eligible, based on the inclusion and exclusion criteria, will be enrolled in the study.

- Hepatitis B immunization status will be recorded on the CRF at study entry.
- All EPI vaccines given throughout the trial will be recorded in the CRF.
- Route of administration: all vaccines will be administered by the intramuscular route to the left deltoid.
- Each child will be observed for at least 60 minutes after vaccination to evaluate and treat any acute adverse events (AEs).
- There will be a 7-day follow-up period for solicited AEs post-vaccination: Day 0 evaluation will be carried out by the study physician at the study center. Subsequently, trained field workers will visit the children to solicit adverse events (AEs) on days 1 to 6 after each vaccination.
- There will be a 30-day (day of vaccination and 29 subsequent days) follow-up after each vaccine dose for reporting unsolicited symptoms.
- Serious adverse events (SAEs) will be recorded throughout the study period. Prior to vaccination, any SAEs due directly to study procedures will be captured. All SAEs will be captured beginning with the administration of the first dose and ending 12 months after Dose 3 of study vaccines.
- All children will be followed by Active Case Detection (ACD) and Passive Case Detection (PCD) for a period extending to one year post Dose 3, ***and then, under a separate consent, until October 2008 in Kilifi and September 2008 in Korogwe.***

***Amended 17 April 2008***

- Two cross sectional surveys for efficacy will be performed at 4½ and 12 months post Dose 3 to determine parasite prevalence, parasite density and hemoglobin, ***and under a separate consent, a third cross-sectional survey for efficacy will be performed in October 2008 in Kilifi and September 2008 in Korogwe to determine parasite prevalence, parasite density and hemoglobin.***

***Amended 17 April 2008***

- In the event that malaria rates are lower in the year of the study the cross sectional survey, unblinding and analysis scheduled at 4½ months post Dose 3 will be delayed until approximately 245 children have experienced an episode.
- Anti-CS antibody titers will be determined at baseline, 1, 4½ and 12 months post Dose 3 ***and under a separate consent, at a cross-sectional survey occurring in October 2008 in Kilifi and September 2008 in Korogwe*** in all study participants.

***Amended 17 April 2008***

- Anti-HBs antibody titers will be determined at baseline, 1 and 12 months post Dose 3 in all study participants.
- CS-specific IFN- $\gamma$  ELISPOT responses will be evaluated at baseline, 1 and 12 months post Dose 3 in study participants at KEMRI, Kenya.
- Regulatory T-cell immune response will be determined at 4½ months post Dose 3 in all study participants.
- Anti-malaria blood stage humoral immunity will be determined at baseline, 1 and 12 months post Dose 3 in all study participants.
- Timing of final analysis is projected for 4½ months post Dose 3. The study will continue in a single-blind manner and be reported as an annex at the end of the study.
- The final analysis is projected to occur after the completion of 4 months of surveillance, at which time it is assumed that 36% of children in the control group will have been affected by a malaria episode. Assuming a true vaccine efficacy of 30%, 400 evaluable subjects per group will have 90% power to detect a difference between the groups using a two sided Fischer exact test with alpha level of 5%.
- The vaccine research teams will ensure that insecticide treated bed net use is optimized in the study population.
- Data collection: conventional Case Report Form (CRF).
- Treatment Groups and vaccination schedule:

| Vaccine        | Regimen       | Number of infants to be enrolled | Estimated number evaluable |
|----------------|---------------|----------------------------------|----------------------------|
| RTS,S/AS01E    | 0, 1, 2-month | 445*                             | 400                        |
| Rabies vaccine | 0, 1, 2-month | 445*                             | 400                        |

\*approximate figure

**Number of subjects**

890 subjects to be enrolled. It is expected that approximately 800 subjects will be evaluable at study end.

**Primary malaria case definition**

- *P. falciparum* infection > 2 500 parasites per  $\mu$ L in a child with a documented fever  $\geq 37.5^{\circ}\text{C}$  (axillary) detected by ACD or PCD.

**Secondary malaria case definition**

- *P. falciparum* infection > 0 parasites per  $\mu$ L in a child with a documented fever  $\geq 37.5^{\circ}\text{C}$  (axillary) detected by ACD or PCD.

**Primary endpoint**

**NOTE:** *In the event that malaria rates are lower in the year of the study the cross sectional survey, unblinding and analysis scheduled at 4½ months post Dose 3 will be delayed until approximately 245 children have experienced an episode.*

**Secondary endpoints**

- Time to first case of malaria meeting the primary case definition over a period starting 14 days after Dose 3 and extending for 4 months.

**Efficacy**

- Time to first case of malaria meeting the secondary case definition over a period starting 14 days after Dose 3 and extending for 4 months.
- Multiple events of malaria meeting the primary case definition over a period starting 14 days after Dose 3 and extending for 4 months.
- Multiple events of malaria meeting the secondary case definition over a period starting 14 days after Dose 3 and extending for 4 months.
- Parasite prevalence and density at 4½ months post Dose 3.
- Hemoglobin at 4½ months post Dose 3.

**Safety**

- Occurrence of solicited symptoms and local reactions over a 7-day follow-up period (day of vaccination and 6 subsequent days) after each vaccination.
- Occurrence of unsolicited symptoms over a 30-day follow-up period (day of vaccination and 29 subsequent days) after each vaccination.
- Occurrence of serious adverse events from the time of first vaccination (Month 0) until 4½ months post Dose 3 (Month 6½).
- Occurrence of parameters of hematological monitoring outside acceptable ranges.

**Immunogenicity**

- Anti-CS antibody titers prior to vaccination, 1 month post Dose 3 and 4½ months post Dose 3.
- Anti-HBs antibody titers prior to vaccination and 1 month post Dose 3.
- Frequency of CD4+ and CD8+ CS-specific T-cells expressing at least two of the following: IL-2, CD40L, TNF-α and IFN-γ prior to vaccination and 1 month post Dose 3.

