### 4.2.2. KEMRI: Malaria Epidemiology

The primary vector of malaria is *An. gambiae*; *An. funestus* also occurs in large numbers in the south of the district. The EIR is estimated to be up to 100 infective bites per person per year [Mbogo 2003]. Transmission of malaria tends to be highest between April and August.

Historically the use of bed nets has been low (<5%). In the last few years however partnerships between various NGOs and the Ministry of Health have enabled the distribution of large numbers of bed nets in the Kilifi District. Recent surveying has shown that among 1 to 5 year old children, bednet use has increased from 35% at the start of 2005 to 70% at the end of 2005.

Malaria is the commonest cause for children under the age of 18 months to be admitted to hospital.

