**5.15.3. Serology and cell-mediated immunity plan**

Serum for antibody determination and blood cells for CMI assessment will be collected by blood sample. Samples for safety will be analyzed at the time they are collected.

Serum samples for anti-CS and anti-HBs antibody titers determination in all study participants will be shipped to GSK Biologicals, Rixensart, Belgium.

Fixed, frozen, antigen-stimulated whole blood samples for CS-specific T-cell immune response assessment (intracellular cytokine staining assay) in all study participants will be shipped to GSK Biologicals, Rixensart, Belgium.

Plasma samples for anti-blood stage humoral immunity assessment from subjects taking part in Tanzania will be shipped to LSHTM and GSK Biologicals, Rixensart, Belgium (or designated collaborating laboratories). Samples may also be tested locally (assay details are provided in Appendix F). Plasma samples for anti-blood stage humoral immunity assessment from subjects taking part in Kenya will be shipped to LSHTM and GSK Biologicals, Rixensart, Belgium (or designated collaborating laboratories). Samples from both Kenya and Tanzania may also be tested locally (assay details are provided in Appendix F).

Amended 23 October 2006.  
Amended 20 November 2006

Assessment of malaria antigen-specific T-regulatory immune responses will be done at both investigator centers (KEMRI, Kenya and JMP, Tanzania).

Assessment of CS-specific T-cells (ELISPOT) will be done at KEMRI, Kenya, on samples from children enrolled at KEMRI, Kenya only (assay details are provided in Appendix F). Amended 23 October 2006.

Any serum or plasma or blood cells not immediately used in immunological assays will be stored at -20°C or less and would only be used to assess the immune response to vaccination or to assess any potential toxicity of the vaccine Amended 23 October 2006.

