## **10.6. Estimated sample size**

### **10.6.1. Power Calculations**

The final analysis is projected to occur after the completion of 4 months of surveillance, at which time it is assumed that 36% of children in the control group will have been affected by a malaria episode. Assuming a true vaccine efficacy of 30% and an attack rate of 36% in controls (corresponding to an attack rate of 25.2% in vaccinees), a sample size of 400 evaluable subjects per group has 90% power to detect a difference between groups using a 2-sided Fisher exact test at 5% significance level. The final analysis is projected to occur after the completion of 4 months of surveillance, at which time it is assumed that 36% of children in the control group will have been affected by a malaria episode. However, in the event that malaria rates are lower in the year of the study, the unblinding and analysis will be delayed until approximately 245 children have experienced an episode ( $400 \times 36\% + 400 \times 25.2\% = 245$ ). This analysis will also have 90% power.

The assumption of 36% attack rate in controls is based on epidemiological data collected at the two sites. In Kilifi the proportion of children aged 12 to 18 months olds affected by a malaria episode using the same ACD methodology as proposed in this document over the same time frame in 2005 was 37% (personal communication [name]). In Korogwe the case rate was 34% determined in children aged 5 to 17 months in Mkokola village (10 km from Korogwe) by Passive Case Detection at village level (personal communication [name], [name]).

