**10.10.3.3. Frequency of T-cells specific to CS**

The frequency of T-cells specific to CS will be identified as CD4/CD8 + T-cells expressing at least two cytokines amongst CD40L, IL-2, TNF- $\alpha$  and IFN- $\gamma$  upon a short term in vitro stimulation with a pool of peptides covering the vaccine CS portion. Results will be expressed as CS-specific CD4/CD8 T-cells per million respectively of CD4 or CD8+ T-cells. Descriptive statistics (N, minimum, Q1, median, Q3, maximum, mean, standard deviation) will be tabulated by group and protection status, for pre and post vaccination timepoints (pre and 1 month post Dose 3) (protected subjects are those recipients of RTS,S/AS01E who are not diagnosed with malaria meeting the primary case definition within the 4½ month ACD period). Analysis by protection status will be limited to recipients of RTS,S/AS01E. Results will also be presented graphically by box plots. Between group comparisons and between protection status comparisons will be performed by non-parametric Wilcoxon Rank Sum tests. Within group comparisons (i.e. comparing post versus pre timepoint within the RTS,S group) will be performed by Wilcoxon Signed Rank test for paired samples.

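### The between-group T-cell test leaves out the pre-vaccination value that the trial collects, and the only test that uses it is a one-arm test that cannot support a vaccine-effect claim

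*Protocol*

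**What the plan says.** The secondary endpoint in the Synopsis and Section 10.2 covers both CD4 and CD8 cells and has two time points: "CS-specific T-cells expressing at least two of the following: IL-2, CD40L, TNF-α and IFN-γ prior to vaccination and 1 month post Dose 3". Section 10.3 repeats it as a tertiary endpoint at 12 months. The trial is a "randomized (1:1 ratio), controlled trial with two groups", and Section 5.15.3 plans "CS-specific T-cell immune response assessment (intracellular cytokine staining assay) in all study participants", so both groups have the pre value for the intracellular cytokine (ICS) assay.

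Section 10.10.3.3 fixes two kinds of test:

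- For the randomised groups, and for protection status: "Between group comparisons and between protection status comparisons will be performed by non-parametric Wilcoxon Rank Sum tests". No baseline term is mentioned for this test.
- For change over time, in the vaccinated group alone: "Within group comparisons (i.e. comparing post versus pre timepoint within the RTS,S group) will be performed by Wilcoxon Signed Rank test for paired samples".

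Section 10.10.3.4 uses the same pair of tests for the exploratory T-cell endpoints, including ELISPOT, which is run at KEMRI only. Section 10.11.3.3 uses them for Clinic Visit 7. In the first two sections the descriptive statistics "will be tabulated by group and protection status, for pre and post vaccination timepoints (pre and 1 month post Dose 3"). Section 10.11.3.3 tabulates Clinic Visit 7 values only.

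**The concern.** Two separate points arise.

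**Precision.** The randomised comparison is written without the child's own pre-vaccination value. If that value predicts the later one, the test discards information already collected in both groups.

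**Interpretation.** The one test that uses the pre value is confined to the vaccinated group. A change there mixes the vaccine with anything else that moved between the bleeds, such as natural sporozoite exposure, age or assay drift. The rabies group could show how large those other changes are, but it is left out of the paired test. A significant signed-rank result could then be quoted as a vaccine response when the design does not support that reading. The risk is greater at Clinic Visit 7, more than a year after the screening sample, because the planned table there does not show the rabies group's pre value beside its later one.

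**Working it through.** **The plan's own figure.** The only power statement concerns the primary malaria endpoint: "a sample size of 400 evaluable subjects per group has 90% power to detect a difference between groups using a 2-sided Fisher exact test" (Section 10.6.1), with 36% against 25.2%. Full enumeration of the Fisher exact test gives 90.2%, and 400 × 0.36 + 400 × 0.252 = 244.8 events. The figure reproduces. No effect size, SD, pre/post correlation or power is stated for T cells, so those below are assumptions, shown over a range.

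**Precision, by formula.** Let ρ be the pre/post correlation. Relative to comparing post values alone, ANCOVA on the pre value multiplies the variance of the group difference by 1 − ρ². If the post-only comparison has 80% power at two-sided 5%, adjusted power is Φ[(1.960 + 0.842)/√(1 − ρ²) − 1.960].

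| ρ | 1 − ρ² | Power | Gain (points) |
|---|---|---|---|
| 0 | 1.00 | 80.0% | 0 |
| 0.1 | 0.99 | 80.4% | 0.4 |
| 0.2 | 0.96 | 81.6% | 1.6 |
| 0.3 | 0.91 | 83.6% | 3.6 |
| 0.5 | 0.75 | 89.9% | 9.9 |
| 0.7 | 0.51 | 97.5% | 17.5 |

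**Precision, by simulation.** Settings: 400 per group, normal scale, true effect 0.2 SD, 2000 runs, so the Monte Carlo error is about √(0.8 × 0.2/2000) = 0.9 points.

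| ρ | Rank-sum on post | ANCOVA | Rank-sum on change |
|---|---|---|---|
| 0 | 79.2% | 80.4% | 50.0% |
| 0.3 | 78.0% | 83.8% | 63.8% |
| 0.5 | 79.0% | 91.3% | 79.6% |
| 0.7 | 79.2% | 97.8% | 94.8% |

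The 1.2-point gap at ρ = 0 is not a baseline gain. It is within what simulation error and the rank test's small loss on normal data can produce. With 350 per group and rank ANCOVA, rank-sum power is about 71–74%. Rank ANCOVA gives about 72–74%, 76–77%, 83–84% and 88–89% at ρ = 0, 0.3, 0.5 and 0.6.

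Testing raw change is not a good substitute. Its variance is 2(1 − ρ) relative to post-only, which is larger than 1 whenever ρ is below 0.5.

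**Validity under exposure common to both groups.** Settings: no vaccine effect, the same natural shift in both groups, ρ = 0.3, 400 per group. The table gives rejection rates.

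| Shift (SD) | Signed-rank, RTS,S only | Rank-sum on post | ANCOVA |
|---|---|---|---|
| 0 | 4.4% | 4.8% | 4.8% |
| 0.1 | 37.2% | 5.2% | 4.6% |
| 0.2 | 91.4% | 4.6% | 4.8% |
| 0.3 | 100% | 5.5% | 5.0% |

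The randomised test keeps its error rate. The one-arm test detects the shift, whatever caused it. With the shift expressed in SDs of the within-child change, 0.1 and 0.2 give about 52% and 97%.

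**The case against.** **The planned randomised comparison is sound.** This stands in full. A reader might infer that, because the between-group test ignores the pre value, natural malaria exposure could pass for a vaccine effect in it. The documents do not support that. The groups are randomised and followed concurrently, so exposure acts on both, and the simulated error stays at 4.6% to 5.5%. Omitting the baseline costs precision and leaves chance imbalance uncorrected; it does not bias the test.

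**The protocol does not call the signed-rank test the measure of vaccine effect.** Also true. It is labelled a within-group comparison and comes after the between-group one. The one-arm rejection rates above are therefore not false-positive rates for any claim the plan makes. They show why that test should not be used for one.

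**Control-group pre and post values are already tabulated.** True for Sections 10.10.3.3 and 10.10.3.4, though as summaries by time point rather than as a paired change, and not true for Section 10.11.3.3.

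**An analysis plan may add the adjustment.** Section 6.5 foresees one, and Section 10.10.3.3 does not name the variable that the rank-sum test is applied to. But Section 10.9.5 leaves covariates to that plan for efficacy only. For T cells the protocol states the tests and chooses which group receives the paired one.

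**The size of exposure between bleeds is unknown.** A reader may want to convert entomological rates into a T-cell shift. For Kilifi, "The EIR is estimated to be up to 100 infective bites per person per year"; for Korogwe, Section 4.1.2 gives around 90. Table 4 allows 0–60 + 21–35 + 21–35 + 21–42 = 63 to 172 days from Clinic Visit 1 to Clinic Visit 5. Spread evenly, that is 63 × 90/365 ≈ 16 to 172 × 100/365 ≈ 47 bites. The Kilifi rate is an upper figure, and nothing in the protocol links bites to T-cell frequency, so this shows that a shift is possible, not how large it is.

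**Conclusion.** The point holds in a limited form. The between-group T-cell test in Sections 10.10.3.3, 10.10.3.4 and 10.11.3.3 is valid but leaves precision unused. From 80% power, the gain from adjustment is negligible at a correlation of 0.2 or less, about 4 points at 0.3 and about 10 points at 0.5, with essentially no loss at 0. These figures rest on an assumed correlation, a normal scale and complete baselines. They do not carry over directly to ELISPOT, which Table 6 limits to 445 children in both groups together.

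The within-RTS,S signed-rank test cannot attribute change to the vaccine and should not support such a claim. Since the endpoint is secondary, tertiary or exploratory and outside the sample size calculation, this is an improvement to consider, not a defect that threatens the trial's conclusions.

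**What to change.** In Sections 10.10.3.3, 10.10.3.4 and 10.11.3.3:

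- State that the vaccine effect on T cells is judged by the between-group comparison adjusted for the pre-vaccination value, using rank ANCOVA or ANCOVA on the log scale. Stratify by site for ICS, since Section 6.4.1 provides a separate randomisation list for each site. ELISPOT needs no site stratification.
- Label the within-RTS,S pre/post result descriptive, and show the same paired summary for the rabies group, including at Clinic Visit 7.

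The change is to wording only; it needs no new samples or visits. The one real cost is missing baselines. Section 10.8 does not replace missing measurements and excludes the subjects concerned, so an adjusted analysis would lose children without a pre value. A simple rule covers this: for example, a missing-baseline indicator, which is acceptable here because the sample is taken at Clinic Visit 1, before randomisation at Clinic Visit 2. Alternatively, keep the unadjusted rank-sum test as a sensitivity analysis.
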